According to a recent individualized-participant data meta-analysis, participants receiving internet interventions based on personalised (normative) feedback are significantly less likely to maintain low-risk drinking patterns at follow-up than those in extended internet programs based on integrated therapeutic principles like Cognitive Behavioral Therapy (CBT) and Motivational Interviewing (MI) [10]. Moreover, guided internet interventions exhibited greater effects on drinking patterns than unguided interventions [10]. However, only one study has directly compared a brief online intervention conceptualised as PNF (Personalized Normative Feedback) and a booklet with an unguided online self-help intervention. Although unguided, the latter was very intense, containing 56 daily sessions plus six weekly follow-up sessions, and involved alcohol misusers from the general population [11]. Although only 8 % completed all sessions in the intensive intervention group, there was a superior reduction in alcohol use in this group than in the PNF/booklet group over the medium term (6 months follow-up).

The goals of the currently-proposed study are to evaluate the efficacy of the adapted *“Selge” program*, in terms of reducing alcohol misuse in Estonians, and to assess its effects on treatment referrals. The intervention is adapted from the integrated alcohol misuse and depression symptoms treatment developed by collaborators [12] and consist of 10 modules based on MI and CBT. We expect that the *„Selge* “*program* will result in greater reductions in alcohol misuse than the control intervention, which will consist of a self test for alcohol abuse and routine advice regarding treatment.

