##### Modules

Ten treatment modules (see Fig. 3) comprise the majority of this 8-week program. Participants are advised to complete the modules at their own pace, but in the order listed. However, they may freely skip or repeat any module, if they choose. The content of each module was created based upon the principles of CBT and MI (Table 1). The emphasis is on strategies to reduce negative thinking and worry, on behavioural activation, and on self-care (e.g., sleep hygiene). A progress bar, also visible on the dashboard, indicates each user’s progress in the module, which is saved page by page.

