##### Control condition

Individuals assigned to the control condition are told that they will have access to the complete program in 6 months. In the interim, they only have access to a help page called “Where to turn”, which lists treatment centers (including contact details), psychiatric care providers and further health services. Moreover, they are advised to visit the website www.alkoinfo.ee [16], where they can learn about the principles of alcohol abuse treatment, complete a self-administered test based on the AUDIT [6] (see Fig. 4), and receive personalized feedback.

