### Sample size calculation

A recent meta-analysis [24] showed that combining CBT and MI resulted in statistically-significant reductions in alcohol use, with effect sizes in the small range for internet interventions (*g* = .20). As we aim to compare the *“Selge” program* with a control condition which provides extensive resources and a self-administered test of alcohol abuse, we expect larger effects. The study that comes closest to our design compared online Personalized Normative Feedback (PNF) plus an intensive, but unguided CBT (56 daily sessions plus six weekly follow up sessions) program versus PNF with an online booklet; it also recruited alcohol misusers from the general population and it generated a Cohens’ *d* = 0.20 [11]. As we are offering a minimal-guidance intervention and comparing it to a self-administered test with routine advice on usual treatment, we expect a Cohens’ *d* = 0.23 for the current study. Using G*Power, the sample size required to detect this small effect with 80% power and α = 0.05 is *N* = 596 total (298 per group).

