### Data analysis plan

All analyses will be guided by the intention to treat (ITT) principle. Preliminary testing will assess two things: differences between the two study arms at baseline; and the degree of missing data. Baseline differences will be analysed by (generalised) linear mixed models (LMM). Missing data will be addressed by multiple imputation procedures from Amelia II through R [25]. Imputed data will be analysed with multinomial and binary regression models, considering two-sided tests with a type I error rate of *p* < 0.05 as statistically significant. Results will be cross-checked with complete case analyses of non-imputed data. Besides ITT analyses, we will also perform per-protocol analyses.

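### A per-protocol set based on programme use has no counterpart among controls; a complier-average effect would answer the adherence question and keep the randomised comparison

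*Protocol article*

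**What the plan says.** The Data analysis plan puts ITT first: "All analyses will be guided by the intention to treat (ITT) principle". It then adds: "Besides ITT analyses, we will also perform per-protocol analyses". The article does not say what makes a participant per-protocol in either arm.

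Four other parts of the article determine what such a set could be.

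- **Treatment condition, Modules and Consumption diary.** The dashboard, diary and ten modules belong to the treatment website. Use is voluntary: participants set their own pace, and "they may freely skip or repeat any module, if they choose".
- **Control condition.** For controls, "In the interim, they only have access to a help page", plus advice to visit a public website. They have no course to complete.
- **Secondary outcomes.** Retention is measured by diary completion. Use of programme resources is asked in the treatment group only. Use of additional resources and of professional help is asked in both groups.
- **Study design.** Allocation is open. Use of usual treatment is assessed in both arms at 8 weeks and 6 months.

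**The concern.** Programme adherence can be observed in one arm only, and it is the participant's own choice after randomisation. People who work through the modules or keep the diary may be more motivated or less severely affected, and might have improved more in either arm. A per-protocol set chosen on programme use keeps these people in the intervention arm. The controls who would have behaved the same way cannot be identified. A precise definition does not help, because any definition based on programme use has the same gap.

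At stake is how a secondary result is read. The Discussion links a favourable finding to continued national implementation and intends the results for the public and policymakers. A per-protocol estimate printed beside a diluted ITT estimate could pass for efficacy among users when part or all of it is selection.

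**Working it through.** **The plan's own figure.** Sample size calculation expects a Cohen's d of "0.23 for the current study" and says that "the sample size required to detect this small effect with 80% power and α = 0.05 is" 596 in total, 298 per group. With the Data analysis plan "considering two-sided tests with a type I error rate of" 0.05, the noncentral t distribution gives power 0.8004 at 298 per arm and 0.7991 at 297. The figure reproduces, so 0.23 SD is a fair yardstick for the bias.

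**Inputs.** From the article: target 600 randomised 1:1 (300 per arm) and expected 6-month follow-up of 40–60% (Discussion), so half followed up is 150 per arm. Assumed: the share p of the intervention arm counted as adherent, and the correlation rho between an adherence score and the outcome.

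**Bias under no treatment effect.** If the adherence score is normal and the top share p is kept, the mean outcome of those kept differs from that of the whole arm by

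bias = rho × phi(z) / p, where z cuts off the upper share p.

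Example: p = 0.3 gives z = 0.524, phi(z) = 0.348 and phi(z)/p = 1.159. With rho = 0.2 the bias is 0.232 SD.

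**False-positive rate.** This is a two-sided t-test at 0.05 with noncentrality bias / sqrt(1/n1 + 1/n0), where n1 = p × n0. Example: 45 against 150 gives 0.232 / sqrt(1/45 + 1/150) = 1.36, which rejects in 27%. For simplicity, all followed-up controls are kept and the SD is taken as 1.

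| Adherent share p | phi(z)/p | Bias in SD at rho 0.1 / 0.2 / 0.3 | False positives, half followed up (n0 = 150) | False positives, full follow-up (n0 = 300) |
|---|---|---|---|---|
| 0.2 | 1.400 | 0.14 / 0.28 / 0.42 | 11% / 29% / 55% | 17% / 51% / 84% |
| 0.3 | 1.159 | 0.12 / 0.23 / 0.35 | 10% / 27% / 53% | 16% / 49% / 82% |
| 0.5 | 0.798 | 0.08 / 0.16 / 0.24 | 9% / 20% / 39% | 13% / 36% / 67% |
| 0.8 | 0.350 | 0.035 / 0.07 / 0.10 | 6% / 9% / 14% | 7% / 13% / 23% |

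**Cross-check with a different model.** Suppose a share a adheres, and adherers do D SD better than non-adherers in either arm. Adherers against all controls then differ by (1 − a) × D. With a = 0.5 and D = 0.3 this is 0.15 SD. At 298 per arm the false-positive rate is about 32% (simulation 32.2%), and at half follow-up about 18.5% (simulation 18.3%). The full-arm comparison in the same simulation stays at 5.2%. With D = 0 there is no bias.

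**The case against.** The strongest reply is that the article defines no per-protocol set, so nothing in it says that all controls are kept. This stands. A reader might infer a comparison of adherent users with every control, but use of other resources and professional help is recorded in both arms, and those data or completion of follow-up could remove controls too. The missing definition is also something an article may leave to the full plan, and it is not criticised here. The reply does not remove the problem: excluding controls for seeking other help selects them on a different behaviour, and the two sets would still not be comparable.

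A reader might also infer that adherence will be rare, because in the closest earlier trial "only 8 % completed all sessions in the intensive intervention group". The article does not support that step. That programme had 56 daily and six weekly sessions, Selge has ten modules and an e-coach, and the authors expect relatively high adherence. If they are right, the bias shrinks, as the last row of the table shows.

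Nor should one cell of the table be read as the error rate. The 49% at full follow-up (30% adherent, rho 0.2) depends on two assumed values and on follow-up that the authors do not expect.

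Finally, ITT leads and no decision rule is tied to the per-protocol result. That limits the consequence and stands in full.

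**Conclusion.** The point holds as a matter of design. In this trial, a per-protocol comparison based on programme use is not a randomised comparison, whatever definition is later written. Its size is uncertain, because neither the adherent share nor its correlation with outcome is in the article. Under the stated assumptions the bias ranges from a third of the planned effect (0.08 against 0.23) to nearly twice it (0.42). It is smaller if most participants adhere and zero if adherence is unrelated to outcome.

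The ITT analysis, and with it the primary conclusion, is untouched. The change is worth making because it is cheap and the alternative uses the same randomised arms.

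**What to change.** In the Data analysis plan, make the supportive adherence analysis a complier-average causal effect: two-stage least squares with randomised arm as instrument, baseline AUDIT as covariate, on the same imputed data sets as the ITT analysis.

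- **Exposure.** Any logged use of the programme: module, diary or e-coach contact. Requiring a completed module would count as untreated some people who used the diary, calculator, dashboard or e-coach, and would strain the exclusion restriction. Automated e-coach e-mails to people who never use the programme remain a possible breach, to be stated.
- **Sensitivity.** A version with number of modules as the exposure.
- **Log check.** Confirm that controls did not use the programme before their 6-month assessment. Study design ties access to completing that assessment, whereas Randomization and trial flow says after 6 months, and a late assessment could fall after that date. Applicants who do not qualify may also use the tool, and an account needs only a username and an e-mail address. One-sided non-compliance should therefore be checked, not assumed.
- **Labelling.** Any per-protocol result still reported is described as non-randomised and supportive, with no efficacy claim resting on it.

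Cost: a wording change and a few lines of code. Module progress is already saved page by page and diary data are available to researchers; e-coach contacts may need to be counted. The confidence interval is wider. For example, if 80% use the programme (an assumption), an ITT effect of 0.23 becomes 0.23 / 0.8 = 0.29 and its standard error grows by about the same factor. The exclusion restriction must be stated, and the analysis inherits the missing-data assumptions of the imputation.

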## Discussion

The planned study will evaluate the efficacy and the potential for referral to treatment as usual of the self-help *“Selge” program* for alcohol misusers and those with likely alcohol dependence in Estonia. This will be the first internet program provided in Estonia with culturally-adapted contents and state-of-the-art design and technology, and will be directly implemented in a larger, country-wide health promotion campaign. This comprises a unique opportunity, from both an intervention and research perspective. Our goals are to achieve maximum attention in the general population of Estonia and reach as many individuals from the target group as possible, similar to a recent screening and brief intervention Website [7] – with most of those in the target population having never received any prior alcohol treatment at all. Most similar programs that were introduce in other countries have had to compete with other already-existing internet programs for the reduction of alcohol misuse, among which most likely had never been evaluated for efficacy, and most lacked evidence-based therapeutic content [26]. Thus, we expect somewhat higher intervention adherence as observed in similar studies in other countries [10, 12]. This is, amongst others, one reason why we decided to have an active control group consisting of a self-administered test as well as advice on and how to access treatment as usual. Such a direct comparison has only been reported for one other study [11], which contained several methodological limitations. If the *“Selge” program* turns out to be effective, it will be continuously advertised and implemented as an important part of the continuum of intervention and care for alcohol misuse and dependence in Estonia. Moreover, maintenance of the program would be guaranteed for system and content updates in the future, a feature that is rarely the case for internet interventions for the reduction of alcohol misuse, due to the inherent limitations of research funds [27].

We chose not to limit our program to harmful and hazardous alcohol users only (AUDIT scores ≥8 and < 20), but also to include alcohol users suggestive of dependence for two reasons. First, we did not want to limit access to the intervention since this is the first program in Estonia of its kind and treatment coverage remains low [5]. Second, we wanted to allow for comparison of our results against other studies, like the one spear-headed by the World Health Organization (WHO) [18].

We have decided to conduct both a post-intervention measurement and a follow-up measurement in order to distinguish the intervention effects from any follow-up effects. However, this can reduce the post-intervention and follow-up survey rates, especially since it is an internet intervention. To minimize the risk of excessive loss to follow-up, we have integrated into our design additional telephone calls. We therefore expect follow-up rates of 50–70% at post-intervention and 40–60% at 6 months follow-up [10, 12].

As with every internet-based program for the reduction of alcohol use, we expect a comparatively-high rate of dropout. However, due to the central implementation of the program in Estonians’ alcohol intervention efforts, its uniqueness in Estonia, and its cultural adaptations which include videos in each module, we expect that treatment adherence will be relatively high and the dropout rate relatively low.

Primary trial findings will be published in open-access journals, so both the public and policymakers in Estonia can learn about the intervention and the study results on 2020. Participant-friendly summaries of trial findings will be published on the program website.

## Data Availability

Anonymized study data will be available upon request. Participant-friendly summaries of trial findings will be published on the program website.

## Abbreviations

RCT: Randomized controlled trial
CBT: Cognitive behavioural therapy
MI: Motivational interviewing
TLFB: Timeline Follow Back
MHI-5: Short version of the Mental Health Inventory
AUDIT: Alcohol Use Disorder Identification Test
NIDA-ASSIST: National Institute on Drug Abuse, Alcohol, Smoking, and Substance Involvement Screening Test
TAI: Tervise Arengu Instituut (Estonian National Institute for Health Development)
PNF: Personalized Normative Feedback
ITT: Intention to treat
GP: General Practitioner
